**Methods:**

Children from the Greater Boston, MA region will be recruited to participate in this single center study. A randomized crossover design will be utilized, such that participants will act as their own controls, through initial randomization to condition assignment and condition counterbalancing across participants. One hundred three children will participate in three randomized acute interventions: moderate intensity treadmill exercise (20 min, 70–75% of their maximal heart rate), seated rest (20 min), and a Trier Social Stress Test for Children (14 min). These visits will occur on 3 three separate days, approximately 5–8 days apart. Before and after each intervention, children complete a variety of cognitive tasks measuring attentional inhibition while their neuroelectric activity is recorded. Variables of interest include EEG data, accuracy and reaction time, academic achievement, and salivary alpha amylase. Academic achievement is also assessed following interventions. In addition, children provide passive drool samples throughout the interventions to measure various biomarkers that may explain the acute exercise benefit on cognition.

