## Material and design

### Summary of aims

The objective of the SNEACY study is to test several aims: (1) Investigate basic laboratory and applied scholastic performance aspects of brain function, cognition, and academic achievement following aerobic exercise compared to active (i.e., Trier Social Stress Test for Children (TSST); a commonly used psychosocial stressor) and passive (i.e., seated rest) control conditions; and (2) Investigate phasic changes in SNS activation (as indicated by sAA) as a potential mechanism for the transient beneficial effect of exercise on brain function, cognition, and academic achievement. Phasic activation refers to brief, rapid changes in the SNS [17] in response to salient or task-relevant information in the stimulus environment [18]. Phasic sAA has been shown to be related with attention, memory, and various academic outcomes [16, 18–22]. SNEACY is a randomized crossover trial with three acute interventions: 20 min of moderate intensity treadmill exercise, 20 min of seated rest, and a 14-min TSST for Children. The TSST and seated rest interventions serve as active and passive control conditions, respectively, for the experimental intervention involving moderate intensity exercise. As a result of this design, changes observed in the aerobic exercise intervention can be attributed to the exercise component of the intervention rather than to other, potentially confounding factors, such as expectancy effects, stress, or elevated heart rate. The study will enroll and randomize 103 typically developing, 9–10-year-old children. We hypothesize that exercise-induced phasic increases in SNS activity, indicated by sAA levels, will mediate the effect of a single bout of exercise on brain function (i.e., P3 amplitude and latency), cognition (i.e., executive control), and standardized achievement test performance (i.e., mathematics, reading). To further explore a relation between exercise-induced change in sAA with brain and cognition, baseline and stress-induced (i.e., exercise, TSST) change in cortisol will be investigated as a potential factor in the analytical model. All participants provide written assent/consent (and legal guardians provide written informed consent) by a trained research technician in accordance with the Institutional Review Board of Northeastern University. The study was designed in accordance with the SPIRIT statement, details are provided in Fig. 1.

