### Recruitment

Recruitment for SNEACY began in February of 2019, and the goal is to enroll 103 (60 female) children by December 2021. Participants are typically developing, healthy 9–10-year-old children from the Greater Boston, MA region. The goal for recruitment of racial and ethnic minorities is in proportion to the demographic representation in Boston, MA (77.4% Caucasian, 13.2% African American, 17.4% Latino/Hispanic, 5.4% Asian, 1.2% Native American, 0.2% Native Hawaiian and Other Pacific Islander, and 2.5% multiracial). Participant recruitment occurs through local media outlets, community websites, parent group website, University list-serves, contact with local youth organizations, and fliers. To recruit racial and ethnic minorities, diverse neighborhoods in the greater Boston area will be a focus of recruitment, particularly in terms of community centers, libraries, and local newspapers. Fliers contain a general introduction of the research and the contact information of the research team so that interested individuals initiate contact with the research team directly. Recruitment, enrollment, and randomization occur continually.

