### Power and analytic strategy

A traditional power analysis was conducted to estimate the appropriate sample size necessary for detecting a mediating effect of sAA levels on the relationship between a single bout of aerobic exercise and acute changes in cognition given the inclusion of potentially confounding variables (e.g., age, sex, BMI, IQ, SES) based on a one-sided alpha of .01 to correct for multiple outcomes and a power of 0.8. For the total effect of exercise on the ERP and cognitive outcomes, an effect size was calculated from the results reported in Hillman et al. [9], which observed increased P3 amplitude, task performance, and scholastic achievement following acute exercise relative to rest in a sample of preadolescent children resulting in a moderate-to-large effect size (Cohen’s *d* = 0.79). Therefore, assuming a medium size of Cohen’s *f*2 = 0.15 for the total effect and 8 predictors (including exercise condition, subject ID, and covariates) in the regression model, power analysis indicate that a sample size of 82 participants will provide adequate power to detect the effects of a single bout of exercise on neuroelectric function and behavioral performance. For the mediation analysis, medium effect sizes [33] were assumed for both the direct effect of exercise on sAA levels (path a: coefficient = a) and the direct effect of sAA level on the outcomes controlling for treatment condition (path b: coefficient = b). Corresponding to Cohen’s [34] criteria for medium (13% of the variance) effect size, the values of a and b were set at 0.39. Applying the Sobel [35] first-order test, the indirect effect or the mediated effect of exercise on outcomes through sAA was indicated by the product of a and b and was tested. Empirical power results [36] showed that a sample size of *N* = 103 per study was required to detect the presence of mediation. Accordingly, we aim to recruit *N* = 120 to account for attrition.

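### Enrolment is set at 103 in two sections, but the power section gives 103 as the number required for the mediation test and 120 as the recruitment target

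*Protocol article*

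**What the plan says.** Power and analytic strategy sizes the mediation analysis and concludes that "103 per study was required to detect the presence of mediation". The next sentence draws the consequence that the trial will recruit "120 to account for attrition". In that section 103 is the number needed after losses and 120 is the number brought in.

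Two other sections use 103 as the intake figure:

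- Summary of aims: "The study will enroll and randomize 103 typically developing" children of the stated age.
- Recruitment: "the goal is to enroll 103 (60 female) children by December 2021".

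The Methods part of the abstract adds that "One hundred three children will participate in three randomized acute interventions". This agrees with an intake of 103, but it could also describe 103 children who complete all three visits.

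Blinding and randomization places randomisation after the first visit. The three intervention visits follow it.

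**The concern.** The same number serves as the size the mediation analysis requires and as the number of children enrolled and randomised. Both can be true only if no child is lost. The power section itself expects losses, and the Discussion names compliance over several visits and sufficient saliva production as challenges. Saliva supplies the mediator, so these losses would fall on the analysis that 103 was meant to support. The Background calls the mediating role of sympathetic activity the primary goal, and Primary outcome repeats the mediation hypothesis.

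At stake is which number governs recruitment. The two targets differ by 120 − 103 = 17 children, and only the larger one leaves room for loss.

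**Working it through.** **Inputs from Power and analytic strategy.** Required number 103; recruitment target 120; "based on a one-sided alpha of .01 to correct for multiple outcomes and a power of 0.8"; for the two mediation paths, "the values of a and b were set at 0.39"; test: "Applying the Sobel [35] first-order test"; 82 children for the total effect. The attrition rate is not stated.

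**Step 1: implied attrition.** 1 − 103/120 = 17/120 = 14.2%. Round rates give nearly the same target: 103/0.86 = 119.8 and 103/0.85 = 121.2. So 120 is a plausible inflation of 103, but the rate can only be back-solved.

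**Step 2: children remaining if 103 are enrolled.** 103 × (1 − d), where d is an assumed loss; the implied rate gives 103 × 103/120 = 88.4.

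**Step 3: Sobel power.** Take unit-variance exposure and residuals and one independent observation per child, so each path has standard error of about 1/√N. With a = b = 0.39 the expected Sobel statistic is ab/√(a²/N + b²/N) = 0.39 × √(N/2), and power = Φ(0.39 × √(N/2) − z), with z = 1.960 for two-sided .05 and 2.326 for one-sided .01.

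The plan's own figure first. Solving for 0.80 power gives N = 2 × ((z + 0.842)/0.39)². At two-sided .05 this is 103.2, which matches the stated 103. At the stated one-sided .01 it is 132.0, which does not. Both levels are therefore shown.

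| Assumed loss from 103 | Remaining N | 0.39 × √(N/2) | Power, two-sided .05 | Power, one-sided .01 |
|---|---|---|---|---|
| none | 103 | 2.799 | 0.80 | 0.68 |
| 5% | 98 | 2.730 | 0.78 | 0.66 |
| 10% | 93 | 2.659 | 0.76 | 0.63 |
| 14.2% (implied) | 88 | 2.587 | 0.73 | 0.60 |
| 20% | 82 | 2.497 | 0.70 | 0.57 |

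A simulated Sobel test (20,000 replicates, continuous exposure, no direct effect) gives 0.88 at 103 and 0.79 at 88 for two-sided .05, and 0.71 and 0.57 for one-sided .01. The levels differ from the closed form, but the direction is the same. The fall from 103 to 88 is about 0.06 to 0.08 by the closed form and 0.09 to 0.15 by simulation.

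**Step 4: the total effect.** The stated 82 reproduces: a noncentral F test with f² = 0.15, one tested degree of freedom, 8 predictors and alpha .01 gives power 0.803 at 82. A remaining 88 exceeds this; a 20% loss (82.4) only just meets it.

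**Step 5: the goal of 60 girls.** 60/120 = 50%; 60/103 = 58%.

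**The case against.** The best reconciliation is that 120 counts children recruited and 103 counts those randomised. It has some basis: IQ and Tanner status are assessed on the first day, and randomisation follows that visit, so more children may be recruited than randomised. But the power section gives attrition, not screening failure, as the reason for 120. If 103 is the number randomised, nothing covers losses over the three visits that come afterwards. The reconciliation does not remove the conflict.

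Other objections stand and limit the point:

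- A reader might infer that recruitment will stop at 103. Recruitment states a goal, not a ceiling or stopping rule, and the power section says 120. If 120 is the working target, this is an editing error that costs no power.
- A reader might infer that the trial will end with 88 children. That number reuses a back-solved rate, and the article gives no attrition rate. It also treats every lost child as absent from the analysis, although the article defines no completers-only set.
- A reader might set 0.60 at one-sided .01 against the planned 0.80 and blame the enrolment figure for the whole gap. Of that 0.20, 0.12 is already present at 103 with no loss at all; only about 0.08 comes from going from 103 to 88.
- The goal of 60 girls is suggestive at most. No section states a target of half girls, so it does not prove that the two totals were mixed up.

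**Conclusion.** The inconsistency is real and lies in current text: Summary of aims and Recruitment set the intake at 103, while Power and analytic strategy requires 103 for the mediation test and plans to recruit 120. The abstract cannot be counted as a clear third instance.

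The consequence is conditional. If 103 is the operative intake, any loss after randomisation takes the trial below its own required number. Under the implied 14.2% loss the deficit is about 15 children, and closed-form mediation power falls by about 0.06 at two-sided .05 or 0.08 at one-sided .01. These figures rest on an assumed attrition rate, on lost children not contributing to the analysis, and on a simple unit-variance approximation with one observation per child. The exposure is confined to the mediation test unless losses reach about 20%. Whether 103 is large enough for the stated one-sided .01 is a separate question, which settling the enrolment figure does not answer.

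**What to change.** State one target in the abstract, Summary of aims, Recruitment, and Power and analytic strategy, and say whether it counts children recruited or randomised. Either:

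1. enrol and randomise 120 to obtain 103 completers, which follows the power section's own plan, and state the attrition rate assumed; or
2. if 103 is the enrolment ceiling, state the assumed attrition and the expected number of completers, and restate the mediation power for that number.

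Then check that the goal of 60 girls fits the total kept.

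The cost is a few edited sentences, plus one power calculation under the second option. The first option needs no enrolment beyond the power section's plan if its 120 means children randomised. If it counts children before the first-day screening, somewhat more would have to be recruited. Neither option cures the separate shortfall at one-sided .01.

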#### Days 2–4 procedure

At intervention visits (days 2, 3, and 4), the participant engages in the same protocol each day, with the sole exception of a different intervention each day. At the start of each visit, children are outfitted with a heart rate monitor to measure the intensity of the intervention. Upon entering the laboratory, children are asked to sit quietly for 10 min to allow their heart rate to return to baseline levels, after which they provide the first saliva sample by drooling into a tube. Participants are then fitted with an EEG cap. Next, they complete cognitive tasks on a computer while EEG data is simultaneously collected. Then, the child completes one intervention at each visit: (1) aerobic exercise, (2) quiet resting, or (3) the TSST. Upon completion of the intervention, participants provide another saliva sample. Participants then complete the same cognitive tasks again while EEG data is simultaneously collected. Participants will provide another saliva sample, and then they will complete an academic achievement test. At the end of the visit, the final saliva sample is collected. Visits 2–4 last approximately 2.5 h each. At the conclusion of study participation, no further ancillary or post-trial care was offered.

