	**Days 2–4 protocol**
0–10 min	10-min rest/baseline
10–25 min	EEG cap preparation
25–30 min	Baseline saliva sample
30–45 min	Pre-intervention cognitive tasks
	Interventions
45–60 min	*Trier*
45–70 min	*Aerobic and rest*
70–75 min	Post-intervention saliva sample
75–90 min	Post-intervention cognitive tasks
90–95 min	Post-cognitive task saliva sample
95–115 min	Academic achievement testing
115–120 min	Intervention completion saliva sample

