#### Academic achievement testing

##### Wide Range Achievement Test 4 (WRAT4)

Participants complete the WRAT-4 assessment tests for reading (the number of words pronounced correctly) and mathematics (the number of mathematical computations completed correctly). The WRAT-4 is a commercially available paper and pencil based academic achievement assessment that has been age normed. The WRAT allows for repeated administration through the use of two equivalent forms. Administration of the WRAT-4 is conducted by trained experimenters with the duration of the assessment lasting ~ 30 min. Each child completes one version of the WRAT-4 following their rest session, and one version of the WRAT-4 following either their aerobic or TSST session, since only two versions of the task exist.

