#### Saliva collection (sAA and cortisol)

Salivary samples for evaluation of sAA and cortisol are collected throughout the experimental manipulation at 4 timepoints. These collection timepoints include: before cognitive testing begins/baseline, following the intervention, following post-intervention cognitive tasks, and at the completion of the visit. At each collection time, participants are seated comfortably, leaning forward with arms crossed in front of them. Unstimulated salivary samples (at least 2 mL) are collected by the passive drool technique over a 2-min period. Samples are collected into pre-weighed saliva collection tubes and immediately placed on ice. After weighing collection tubes for quantitation of saliva volume and determination of flow rate ([post-collection tube weight − pre-collection tube weight]/2 min), samples are aliquoted and frozen at − 80 °C until analysis. sAA and cortisol are packaged, shipped on dry ice, and analyzed at the University of Ottawa. sAA and cortisol are measured using commercially available kits (α-amylase Saliva Enzymatic Assay and Cortisol Saliva ELISA, IBL International, Hamburg, Germany) according to manufacturer’s instructions. Briefly, on the day of analysis, saliva samples are thawed, centrifuged at 1500×*g* for 15 min at room temperature to remove cellular contaminants and debris. For sAA, samples are diluted 1:301 in diluted sample buffer, and read in a microplate reader (POLARstar Omega, BMG Labtech, Guelph, Canada) at 22 °C at a wavelength of 405 nm at 3 and 8 min after incubation at room temperature. For CORT, samples are incubated with enzyme conjugate solution at room temperature for 2 h, washed, incubated with enzyme substrate solution at room temperature for 30 min. After the addition of the “Stop Solution” to end the enzyme/substrate reaction, samples are read in a microplate reader (POLARstar Omega, BMG Labtech, Guelph, Canada) at 450 nm within 15 min. All samples are analyzed at least in duplicate.

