We will investigate whether the effect of the experimental conditions (*x*) on brain function, cognition, or academic achievement (distal *y* outcomes) is mediated by sAA and CORT baseline levels (*i*) and sAA change (*s*) using a path modeling framework (Mplus v8) and conventional model-to-data fit indices [37]. Each model will be adjusted for the set of potentially confounding variables (e.g., age, sex, BMI, IQ, SES). We will interpret significant direct effects on each outcome as supporting our hypotheses. We aim to incorporate the change process of sAA (*s*) and CORT (*s*) within the same model (allowing s and s to covary). We will utilize the most current and recommended practices [38, 39] for testing moderated mediation framework that leverages the stability of the entire sample for model estimation (causal structure); 5000 bootstrap draws will be run to collect the bias-corrected bootstrapped confidence intervals (95% CI) and significant indirect effects will be decomposed in Mplus output (identical to the Sobel test [35]). If mediation is found, subsequent tests of moderation will be conducted. To test the effect of the treatment condition (i.e., exercise, TSST-C, rest) on univariate continuous outcomes (brain function, cognition, academic achievement), three separate models will be tested using planned comparisons with imposed group invariance constraints. Group comparisons in sAA mean can be simultaneously compared (Is sAA larger in exercise compared to TSST-C and/or rest?), while also comparing benefits in the continuous outcomes regressed on sAA.

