## Discussion

The SNEACY study is a large, ongoing randomized crossover trial with a goal of investigating phasic changes in SNS activation (indicated by differential sAA and CORT trajectories) as a potential mechanism for the transient beneficial effect of moderate intensity exercise on brain function, cognition, and academic achievement in cognitively normal children. We predict that following the cessation of moderate intensity exercise performance on executive function tasks will improve, with enhanced neuroelectric functioning and that these improvements will be linked to changes in sAA. In addition, both sAA and cortisol are expected to increase in response to both exercise and the TSST-C in children. This is a well-designed and controlled study, with the exercise prescription individualized to each child reflecting their specific moderate intensity exercise. We further predict that academic performance will be greatest following exercise.

While this is a well-designed, detailed study, it is not without its limitations. The findings from this study will not allow us to determine whether different doses of exercise (i.e., duration, intensity, etc.) result in differences is neuroelectric profiles and cognition. However, we do expect to observe differences in performance based on an individual’s fitness and body composition. Our active control intervention is designed to increase psychosocial stress for the participants, and to increase their heart rate as a result. However, our passive control group is seated at quiet rest and prior research does not indicate cognitive benefits following seated rest [8–10]. In this sense, this is a well-controlled study with the inclusion of positive (TSST-C) and negative (seated rest) conditions. Finally, it would be impossible to measure all individual differences across our participants, which could influence their performance following interventions. There are several challenges that large-scale studies such as this one face. Primarily, ensuring accurate saliva measures from children may be a challenge, and relies on day of pre-intervention compliance from children and their parents. In addition, children must produce enough saliva in a set amount of time. Maintaining compliance and interest over a number of visits for children may be challenging as well.

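### The sAA change factor that serves as mediator is not limited to saliva samples taken before each outcome, and two of the four samples follow the cognitive and ERP tasks

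*Protocol article*

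**What the plan says.** The Summary of aims and Primary outcome sections hypothesise that a short-lived rise in sAA caused by exercise carries the effect of exercise on P3, executive control and achievement. Under Power and analytic strategy, the plan asks whether the effect of condition on all three outcome domains "is mediated by sAA and CORT baseline levels (*i*) and sAA change (*s*) using a path modeling framework". It adds that the sAA and cortisol change processes should enter the same Mplus model and be allowed to covary, with model fit judged by the usual indices. It does not say which samples form *s*, what time loadings apply, or whether *s* differs by outcome. The Discussion describes the phasic change as "indicated by differential sAA and CORT trajectories) as a potential mechanism".

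Saliva is "collected throughout the experimental manipulation at 4 timepoints", namely "before cognitive testing begins/baseline, following the intervention, following post-intervention cognitive tasks, and at the completion of the visit". Table 2 gives the clock times.

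On the academic test, the Days 2–4 procedure section says that "the participant engages in the same protocol each day, with the sole exception of a different intervention each day", and Table 2 shows an academic test in the common visit schedule. The WRAT4 section instead gives each child one version after rest and "one version of the WRAT-4 following either their aerobic or TSST session, since only two versions of the task exist".

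**The concern.** A mediator has to come before the outcome it is meant to explain. For P3, reaction time and accuracy, only the first post-intervention sample lies between the intervention and the outcome. Later samples can be affected by the tasks themselves: the Summary of aims says that phasic sympathetic activity responds to stimuli relevant to the task. If those samples help to measure *s*, effort or performance on the tasks can create an association between *s* and the outcome that is read as path b. Bootstrap intervals and baseline covariates such as age or IQ do not restore the time order. Conversely, a true brief rise seen only in the first post-intervention sample could be diluted. Mediation by sAA is the study's stated primary goal, so the definition of *s* matters.

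The last sample has a further difficulty. It does not follow the same events at every visit, because by the WRAT4 section not every visit includes the test.

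**Working it through.** **1. Order of events (Table 2).**

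| Event | Minutes | Midpoint |
|---|---|---|
| S1, "Baseline saliva sample" | 25–30 | 27.5 |
| Pre-intervention tasks | 30–45 | |
| Intervention | 45–60 (TSST) or 45–70 | |
| S2, "Post-intervention saliva sample" | 70–75 | 72.5 |
| Post-intervention cognitive/ERP tasks | 75–90 | |
| S3, after the cognitive tasks | 90–95 | 92.5 |
| Academic test | 95–115 | |
| S4, end of visit | 115–120 | 117.5 |

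The count of four agrees with the Saliva collection section. S3 and S4 follow the cognitive/ERP outcome; only S4 follows the academic outcome.

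**2. Does the wording call for more than S1 and S2?** An intercept-and-slope growth model fitted to two occasions of one visit has 2 means + 3 variances and covariances = 5 observed moments. It needs at least 2 factor means + 2 factor variances + 1 factor covariance + 1 residual variance = 6 parameters. Unless the residual variance is fixed, it is not identified. A growth model for one visit therefore needs S3 or S4, both of which come after the cognitive/ERP outcome. Freeing the loadings changes the weights but not this order.

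**3. Weights if *s* is a linear slope (assumption).** The weight of sample j is (t_j − mean t) / Σ(t − mean t)².

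- Mean t = (27.5 + 72.5 + 92.5 + 117.5)/4 = 77.5.
- Deviations: −50, −5, +15, +40. Sum of squares: 2500 + 25 + 225 + 1600 = 4350.
- Weights per minute: −0.01149, −0.00115, +0.00345, +0.00920.
- Shares of absolute weight (total deviation 110): S1 45.5%, S2 4.5%, S3 13.6%, S4 36.4%. S3 and S4 together have 50%.

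With equally spaced loadings 0, 1, 2, 3 the deviations are −1.5, −0.5, +0.5, +1.5, and S2 has 0.5/4 = 12.5%, again negative.

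**4. What such a slope does with a pulse.** Slope times the 90-minute span:

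- Rise at S2 only (0, 1, 0, 0): −5/4350 × 90 = −0.10; with equal spacing −0.30.
- Rise at S3 and S4 only (0, 0, 1, 1): 55/4350 × 90 = +1.14; with equal spacing +1.20.
- Rise at S2, half left at S3 (0, 1, 0.5, 0): 2.5/4350 × 90 = +0.05.

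**5. Sensitivity of the S2 share.** The article places the baseline sample differently in different sections, and one paragraph under Saliva collection can be read as five samples.

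- Baseline at 10 min (before cap fitting, as in Days 2–4 procedure): 0.5%, negative.
- TSST sample taken straight after that intervention (62.5 min): 10.4%, negative.
- Five samples: 4.7%, positive.

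S2 stays at 12.5% or less in every variant. The negative sign holds in all four-sample variants but not with five.

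**6. WRAT-4.** By the WRAT4 section each child takes two tests over three intervention visits. For 103 children that is 206 tested visits out of 309; the 103 untested visits are all aerobic or TSST visits. S4 thus follows a test at every rest visit but only at some of the others.

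**The case against.** A reader might infer that the plan defines sAA change as a straight-line slope over four samples. It does not say so. A simple S2 − S1 difference, or the first segment of a piecewise model, would fit the text and avoid the problem; the hypothesis of a brief exercise-induced rise even favours such a reading. The sample-by-outcome rule may stand in a full protocol or SAP that is not shown. Poor fit of a straight line might also be noticed through the fit indices. Later samples have proper uses: S3 precedes the academic test, and cortisol responds more slowly. All of this stands, and it makes the weights in steps 3–5 conditional.

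It does not remove the point. Intercept and change factors, covarying change processes, fit indices and the trajectory wording together describe a growth model, and by step 2 such a model draws on post-outcome samples for P3 and cognition. The article also applies one mediator to outcomes measured at different times.

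A second objection concerns the remedy. The pre-intervention tasks (30–45 min) lie between S1 and S2. They end 25 minutes before S2 (45 to 70), just as the post-intervention tasks end 25 minutes before S4 (90 to 115). If tasks can affect S4, they can affect S2. This is right: S2 − S1 is safe only with adjustment for pre-intervention performance.

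A reader might also want a false-mediation rate. For a linear slope, assuming that task performance feeds into the later samples with coefficient 0.20 to 0.39, simulated rates run from about 0% to 90%, depending on assumed sAA noise, condition coding and number of rows. The documents give none of these, so no rate is claimed.

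**Conclusion.** The point holds in conditional form. It is documented that two of the four samples follow the cognitive/ERP outcome, that one follows the academic outcome, and that the analysis section does not tie the mediator to earlier samples. If *s* uses all four samples, an indirect effect on P3 or cognition cannot be separated from an effect of the tasks on sAA. If *s* is also linear in clock time, the one sample that matters most has about 4.5% of the absolute weight with a negative sign, and half the weight falls after the outcome. The first condition is the natural reading of the wording; the second is an assumption.

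Two stronger readings are not supported. One is that the primary mechanistic question cannot be answered: the necessary samples, S1 and S2, are already collected. The other is that the missing WRAT-4 biases the exercise–rest contrast by a known amount: neither the effect of the test on sAA nor the split between aerobic and TSST visits is given. The contradiction between the WRAT4 section and the Days 2–4 procedure section is real whatever *s* turns out to be.

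**What to change.** - For P3, reaction time and accuracy, define the mediator as the change from the pre-intervention sample to the first post-intervention sample, and adjust for pre-intervention task performance and P3, which are already collected.
- For the WRAT-4, use samples 1–3 at most.
- Keep the four-sample trajectory as a secondary or descriptive analysis.
- Reconcile the statement that all visits share one protocol with the WRAT4 section. In any analysis that uses sample 4, include an indicator for whether a WRAT-4 preceded it.
- Reconcile the number of samples and the place of the baseline sample (before or after cap fitting) across the Days 2–4 procedure, Table 2 and Saliva collection sections.

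The cost is a change of wording in the analysis plan, made before the data are analysed. The drawback is a somewhat noisier mediator, because fewer samples define it.
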